### Data management and statistical analysis

All data will be directly recorded in the online database (www.wjx.cn, Ranxing information technology co., Ltd., Changsha, China). The database system automatically saves the data and ensures the safety, integrity and consistency of the data. The web server is hosted in Alibaba Cloud (Alibaba Group, Hangzhou, China) and is protected by a corporate firewall, while a daily backup mechanism can ensure data security. Data has multi-level permission settings and password protection to ensure data security. In statistical analysis, general statistical analysis will be carried out by using standard statistical software and professional statistical software.

Analysis of Variance (ANOVA) will be used to find out whether there have differences between the AIDS Fighter · Health Defense intervention groups and the control groups in AIDS-related knowledge scores and attitude scores after the intervention of four weeks. Repeated Measures ANOVA will be used to see whether there have differences on the incidence of AIDS-related behaviors followed up for three and six months after the intervention in four arms. Intention-to-treat analysis will be used to account for the influence of attrition. The difference was statistically significant when *P* ≤ 0. 05.

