**Methods:**

A protocol for conducting a randomized controlled trial to evaluate the “AIDS Fighter · Health Defense”, a game-based AIDS education project aimed at improving the ability of adolescents to prevent AIDS. During the four-week intervention, participants will receive: 1) A virus combat game; 2) Goal setting to eliminate HIV; 3) Questions to be answered to be resurrected in the game; 4) Points ranking; 5) Recognition and Rewards. The primary outcomes include changes in participants’ knowledge, stigma attitude, and risk behaviors attitude related to AIDS after four weeks of intervention. The secondary outcomes are the participants’ AIDS-related risk behaviors three and six months after the intervention.

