## Methods/design

### Study design

Study participants will be recruited from adolescent volunteers and allocated to one of the four randomized groups after completing a baseline survey (Fig. 1) (AIDS Fighter · Health Defense intervention group 1; AIDS Fighter · Health Defense intervention group 2; control group 1; control group 2). Participants are required to complete the assessment four weeks later and three-month, six-month follow up visit after the intervention. Our hypotheses are:
There is no statistical difference between AIDS Fighter · Health Defense intervention group 1 and AIDS Fighter · Health Defense intervention group 2 in AIDS-related knowledge, stigma attitude, risk behaviors attitude and the incidence of risk behavior;Compared with adolescents in the control groups, those in the AIDS Fighter · Health Defense intervention groups will have More AIDS-related knowledge, less AIDS-related stigma and fewer AIDS-related risk behaviors.Comparison between control group 1 and control group 2, group 1 will show better effects in improving AIDS-related knowledge, attitude and behaviors.

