### Intervention group: overview

#### AIDS fighter · health defense intervention group 1

Participants will receive the educational game “AIDS Fighter · Health Defense” and will be required to play the game and learn AIDS education essays or videos in the “knowledge corner” at least 5 days a week and 20 min a day. A data management system will be used to monitor the time participants played in the game, and whether they have learned the content in the “knowledge corner”. After four weeks of intervention, the effect of the intervention will be evaluated by using the same questionnaire as applied in the baseline survey.

Participants will be informed that they will be recognized and rewarded after completing daily game tasks and completing four-week follow-up assessments according to the points ranking. The top 20% will receive a “Gold Award” and 50 RMB in cash, the middle 30% will receive a “Silver award” and 50 RMB in cash, and the lowest 50% will receive a “Bronze award” and 20 RMB in cash.

#### AIDS fighter · health defense intervention group 2

Participants will receive “AIDS Fighter · Health Defense”, without limitation in time to play the game or learn the content of the “knowledge corner”, and there are no incentives as recognition or rewards. Participants play this game according to their preference. Four weeks later, the same questionnaires will be used to measure the effect of their use of the game.

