### Recruitment, randomization, and allocation concealment

#### Recruitment

Participants will be recruited through online recruitment and on-site recruitment. The sufficient statistical power to detect changes in AIDS knowledge, attitude and behaviors after the intervention are considered in sample size calculation, and131 participants are need in each group to maintain 80% statistical power. Assuming the attrition rate is 10%, the sample size of each group is determined to be 145, and the total sample size is 580.

The study site is Luzhou City, Sichuan Province, China. Participants will be recruited from secondary school, high school, college and university. When they agree to participate in the research and complete the follow-up measurement and informed consent form will need to be signed for confirmation. After completing the research, each participant will receive a reward of 30 RMB in cash.

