### Outcomes and data collection

The primary outcomes are AIDS-related knowledge, AIDS-related stigma attitude and AIDS-related behaviors attitude before and four weeks after the intervention. AIDS-related knowledge will be assessed through a self-made questionnaire with a total of 45 items, one point for a correct answer. The higher the score, means the more knowledge participants have learned. AIDS-related behaviors attitude will be assessed through a questionnaire with eight items, with one point for a correct answer. The higher the score, means the lower the risk of AIDS-related behaviors among participants. Five experts were invited to verify the content validity of these questionnaires, the item-level CVI (I-CVI) and the scale-level CVI (S-CVI) are both 1. 00. AIDS-related stigma attitude will be assessed through the Chinese version of Zelaya’s HIV/AIDS Stigma Scale, which was compiled by Zelaya [16], with 24 items in total, and was Sinicized by Xing Haiyan [17]. After Sinicization, the I-CVI was 0. 82 ~ 1. 00, and the S-CVI was 0. 97. Each item uses a score of 1–5. The higher the score, the more the participants’ stigma of AIDS.

Secondary outcomes are the AIDS-related behaviors followed up for three and six months after the intervention. Participants will receive cash rewards after completing the evaluation. AIDS-related behaviors will be assessed through the Questionnaire on the Health of Young Students that was issued by the Chinese Center for Disease Control and Prevention, which has 33 items and is the official questionnaire for the investigation of AIDS-related behaviors among adolescents in China. The fewer AIDS-related risk behaviors, the more the participants have gained AIDS prevention capabilities.

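### The primary ANOVA compares four-week scores alone, although the outcomes are defined as changes and baseline scores are collected; adjusting for baseline would gain precision at no data cost

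*Protocol article*

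**What the plan says.** The Methods paragraph of the abstract states: "The primary outcomes include changes in participants’ knowledge, stigma attitude, and risk behaviors attitude related to AIDS after four weeks of intervention". Outcomes and data collection likewise defines the primary outcomes at two time points, listing "AIDS-related stigma attitude and AIDS-related behaviors attitude before and four weeks after the intervention" alongside knowledge.

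Baseline data come before allocation: under Study design, participants are "allocated to one of the four randomized groups after completing a baseline survey". For intervention group 1, the Intervention group overview says that "the effect of the intervention will be evaluated by using the same questionnaire as applied in the baseline survey", and the text for intervention group 2 also refers to the same questionnaires.

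Data management and statistical analysis then names ANOVA to compare the intervention and control groups on "knowledge scores and attitude scores after the intervention of four weeks". Repeated measures ANOVA is named only for the secondary behaviour outcome at three and six months.

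On the population, Recruitment says: "Participants will be recruited from secondary school, high school, college and university". Study participants sets the age range at 15 to 24 years. The randomisation section describes 580 envelopes, 145 per group, and no stratification.

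**The concern.** The outcome is defined with baseline and the analysis is stated without it. This is more than a covariate list left to a later document. The article commits to a specific method for the primary outcomes, at a specific time point, and keeps its longitudinal method for the secondary outcome. Read as written, the primary comparison uses the four-week scores only.

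Two things are at stake. First, precision: whatever part of the four-week score is predictable from the same person's baseline score stays in the error term. Recruits range from secondary school to university, so prior knowledge can reasonably be expected to differ between them and to carry over to a repeat of the same test, although the article gives no data on this. Second, chance imbalance: allocation is unstratified, so the arms may differ at baseline by luck, and an unadjusted comparison passes the predictable part of that difference into the estimated effect.

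**Working it through.** **Inputs from the article.** 131 evaluable per group for 80% power; 10% attrition; 145 per group; 580 in total; significance at 0.05.

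**Assumptions.** Two-sided test (sidedness is not stated). Correlation r between baseline and four-week score of 0.3, 0.5 or 0.7 (none is given). For change scores only, equal standard deviations at the two time points.

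**1. The plan's own figures.** 131 × 1.10 = 144.1, rounded up to 145, and 4 × 145 = 580, as stated. (Dividing instead, 131/0.9 = 145.6, gives 146; the difference is immaterial here.) The 131 itself cannot be reproduced because no effect size or standard deviation is given. Solving backwards for a pairwise comparison:

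d = (1.960 + 0.842) × √(2/131) = 2.802 × 0.1236 = 0.346 SD

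The noncentral t version gives 0.3475. For a four-group F test with 524 analysed, the corresponding effect is f = 0.145.

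**2. Effect of baseline adjustment.** ANCOVA multiplies the error variance by 1 − r². Power is Φ(2.802/√(1 − r²) − 1.960). The sample size that unadjusted ANOVA would need to match ANCOVA at 131 per group is 131/(1 − r²). The sample size that ANCOVA needs for 80% power is 131 × (1 − r²).

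| r | 1 − r² | Variance cut | Power at 131 per group | Unadjusted n to match | ANCOVA n for 80% |
|---|---|---|---|---|---|
| 0.3 | 0.91 | 9% | 83.6% | 144 | 120 |
| 0.5 | 0.75 | 25% | 89.9% | 175 | 99 |
| 0.7 | 0.51 | 51% | 97.5% | 257 | 67 |

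The four-group F test gives 84.0%, 90.8% and 98.2%, so the result does not depend on using a pairwise comparison.

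**3. Would plain change scores do as well?** Their variance factor is 2(1 − r): 1.4, 1.0 and 0.6. Power at 131 per group is 65.8%, 80.0% and 95.1%. Change scores gain over the four-week score only if r exceeds 0.5, and they are below ANCOVA at each r shown.

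**4. Chance imbalance.** With 145 per arm, the standard error of a pairwise baseline difference is √(2/145) = 0.117 SD, so its 95% range is ±1.96 × 0.117 = ±0.23 SD. An imbalance at that limit shifts the unadjusted four-week difference by r × 0.23, which is 0.07, 0.12 or 0.16 SD. Relative to the implied effect of 0.346 SD, that is 20%, 33% or 47%.

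**The case against.** The article is condensed, and it does not expressly exclude baseline. Its wording about changes suggests that the authors mean to use baseline scores, and an analysis plan that is not shown may do so. Because allocation is random and follows the baseline survey, the arm difference in four-week scores and the arm difference in change have the same expected value. The mismatch is therefore one of wording and precision, not of the effect being estimated. The planned ANOVA is unbiased on average with correct type I error, and its standard error already allows for chance imbalance. The size of the gain rests on an assumed correlation: a restricted baseline range, or an eight-item scale such as the one for risk-behaviour attitude, could make it small. At r = 0.3 the gain is under four percentage points. The 80% starting point is itself back-solved.

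Most of this stands as a limit on the claim. It rules out any suggestion of bias or invalidity and makes the size conditional. It does not remove the point. The method is stated, not left open, and as stated it does not use a covariate that is already collected and is defined as part of the outcome. A fuller plan that adjusts for baseline would still leave the published sentence in need of correction.

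**Conclusion.** The concern holds. The stated primary analysis does not match the outcome definition and forgoes precision on all three primary outcomes. Under assumed correlations of 0.3 to 0.7, error variance is 9% to 51% lower with adjustment, and power moves from 80% to between 83.6% and 97.5% at the effect implied by 131 per group. The direction holds for any material correlation; the size depends on r and on that back-solved effect. The planned ANOVA remains valid, so this is a correction that should be made, not a flaw that invalidates the trial.

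**What to change.** In Data management and statistical analysis, replace the ANOVA sentence with: each of the three primary outcomes will be analysed by ANCOVA, with the four-week score as response, and arm and the baseline score of the same scale as terms; adjusted mean differences between arms will be reported with 95% confidence intervals.

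This also settles the wording. With baseline in the model, analysing the four-week score or the change gives the same arm difference, so the outcome definition and the analysis then agree. Do not simply switch to unadjusted change scores, for the reason in step 3 of the working.

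Education level (secondary school, high school, college, university) is a sensible second covariate. The figures above do not depend on it, and the article does not list it among recorded baseline variables, so confirm that it is captured.

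The cost is one sentence. Baseline scores are already collected, and neither the sample size nor the visit schedule changes.

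### Repeated-measures ANOVA is a poor fit for the incidence of risk behaviours, and it fits the stated intention-to-treat analysis only if missing visits are imputed

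*Protocol article*

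**What the plan says.** All references are to the protocol article.

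- **Endpoint.** Outcomes and data collection: "Secondary outcomes are the AIDS-related behaviors followed up for three and six months after the intervention". They come from a 33-item questionnaire. The section explains how the knowledge, attitude and stigma instruments are scored but gives no score for this one, only the direction: "The fewer AIDS-related risk behaviors, the more the participants have gained AIDS prevention capabilities". The first hypothesis under Study design calls the endpoint an incidence: "risk behaviors attitude and the incidence of risk behavior".
- **Method.** Data management and statistical analysis: "Repeated Measures ANOVA will be used to see whether there have differences on the incidence of AIDS-related behaviors", for behaviours "followed up for three and six months after the intervention in four arms".
- **Attrition.** The next sentence reads: "Intention-to-treat analysis will be used to account for the influence of attrition". No imputation, likelihood-based method or complete-case rule is named.
- **Size.** Recruitment gives 131 before attrition ("participants are need in each group to maintain 80% statistical power"), one attrition rate of 10%, and 145 per arm, 580 in all. Behaviour is among the outcomes this calculation is said to cover.

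**The concern.** The method is fixed by name, so this is not a detail left to a fuller document. Two things do not fit.

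1. **Outcome type.** Repeated-measures ANOVA models means of a roughly normal score with constant variance. The variance of a yes/no outcome depends on its level, and the natural summaries are risks, risk differences and ratios. A count of risk behaviours, probably with many zeros, is no closer to the assumed form.
2. **Missing visits.** Classical repeated-measures ANOVA needs both visits from each participant. Intention-to-treat settles who is analysed and in which arm; it does not supply an outcome that was never recorded. The attrition sentence therefore credits intention-to-treat with something it cannot do alone.

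All three hypotheses mention behaviour. What is at stake is whether those comparisons rest on everyone randomised or on a self-selected subset, and whether the result comes out in a form a reader can use.

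**Working it through.** **Inputs from the article:** 4 arms, 145 per arm, 131 per arm needed, 10% attrition, two post-intervention visits, 5% significance level. **Assumed, because the article gives no figure:** the pattern of missingness over the two visits, the incidence of risk behaviour, and any link between behaviour and dropout.

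**1. The plan's own figure.** 131 / (1 − 0.10) = 145.6, and 131 × 1.10 = 144.1, which rounds up to 145. The planned 145 is reproduced to within one participant, and 4 × 145 = 580. The 131 cannot be reproduced, because the article states no effect size, standard deviation or rate. No behaviour-specific power is therefore computed here.

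**2. Participants kept when both visits are required.** With a proportion q missing per visit, 145 × (1 − q)² remain per arm if the visits are missed independently, and 145 × (1 − q) if the same people miss both.

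| Assumed missingness | Complete cases per arm |
|---|---|
| Same 10% miss both visits | 145 × 0.90 = 130.5 |
| 5% per visit, independent | 145 × 0.9025 = 130.9 |
| 10% per visit, independent | 145 × 0.81 = 117.5 |
| 20% per visit, independent | 145 × 0.64 = 92.8 |

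At 10% independent missingness, 580 × 0.81 = 470 participants have both visits, while 580 × (1 − 0.10²) = 574 have at least one. A model that uses available visits would keep the 574. If the same people miss both visits, 580 × 0.90 = 522 contribute under either approach, and a change of model recovers nobody.

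**3. False-positive rate.** Repeated-measures ANOVA was simulated on 0/1 data with no true difference: 4 arms of 145, two visits, complete data, 4000 runs, assumed incidences.

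| Incidence | Arm test | Arm × visit test |
|---|---|---|
| 1% | 3.8% | 3.1% |
| 2% | 4.5% | 4.0% |
| 5% | 5.1% | 5.1% |
| 10% | 5.2% | 4.9% |
| 20% | 4.9% | 5.2% |

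Against a nominal 5% there is no inflation, and the tests are conservative for rare behaviours. This covers only arms of equal size that share one incidence.

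**4. Selection.** Suppose the true incidence is 10%, and 30% of those with the behaviour drop out against 8% of those without. Overall dropout is 0.10 × 0.30 + 0.90 × 0.08 = 10.2%, close to the planned rate. The incidence among those who remain is (0.10 × 0.70) / (0.10 × 0.70 + 0.90 × 0.92) = 0.070 / 0.898 = 7.8%. The observed odds are multiplied by 0.70 / 0.92 = 0.76. If every arm follows the same pattern, the odds ratio is unchanged but risks and risk differences are not. If the pattern differs by arm, every contrast is biased.

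**The case against.** The strongest reply is that the article states no complete-case rule. Its attrition sentence signals an intention to keep all randomised participants, and imputing missing visits before the ANOVA would make the two sentences agree. That step may sit in a fuller document that is not shown. This stands: the sentences are compatible on a condition the article does not state, and calling them a contradiction goes too far.

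Several stronger readings are also tempting and fail:

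- *The test is invalid.* The simulation gives no support for an inflated false-positive rate with equal arms. A 5% and a 20% incidence have variances of 0.0475 and 0.16, a 3.4-fold ratio, but both incidences are assumed and the ratio does not establish harm.
- *The analysis would miss a constant benefit.* The arm × visit term is zero when the effect is the same at months 3 and 6, but the article does not name that term as its test. The arm main effect, averaged over both visits, would pick up such a benefit.
- *No risk difference is available.* If the outcome is coded 0/1, the cell means are proportions and their contrasts are risk differences. Ratios need another model. The effect scale is poorly matched, not absent.
- *The sample falls to 117 per arm.* The article gives one attrition rate, not a rate per visit. If it means loss from the study, so that the same people miss both visits, about 130 remain, which is essentially the target.
- *The endpoint is certainly binary.* Incidence points that way, but the outcomes section speaks of fewer behaviours, so a count per participant remains possible.

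What the reply does not answer is that the named method suits neither a binary outcome nor a count well, and that intention-to-treat by itself does not deal with missing outcomes.

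**Conclusion.** The point holds in a limited form. The article fixes a method for continuous scores for an outcome it calls an incidence, and relies on intention-to-treat for a task that needs a missing-data method. The consequences are lost participants, possible selection bias and an awkward effect scale. Complete cases range from about 130 to 93 per arm over the assumed patterns from 10% missing in the same people to 20% missing independently at each visit. At the favourable end the loss against 131 is negligible. The 7.8% against a true 10% only illustrates selection under assumed dropout rates; the article contains nothing to show it would occur.

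A reader might infer that the trial's main result is in doubt. The documents do not support that: behaviour at months 3 and 6 is secondary, and the four-week knowledge and attitude scores are analysed separately. Severity is should-fix.

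**What to change.** 1. **Define the endpoint:** any risk behaviour (yes/no) over a stated period, or a count, with the contributing questionnaire items listed.
2. **Replace the ANOVA** with a GEE or mixed-effects logistic or log-link model (a count model if the endpoint is a count). Include arm, visit and arm × visit, and adjust for baseline behaviour where collected. Use every available visit of all randomised participants in their allocated arm.
3. **Report** the between-arm risk difference or ratio with its confidence interval at each visit (a rate ratio or mean difference for a count). With a mixed logistic model, obtain risks by averaging predictions over participants.
4. **Replace the attrition sentence** with the analysis set, a method valid when data are missing at random, and one sensitivity analysis. A mixed model fitted by likelihood meets the second requirement directly. A plain GEE on available visits needs a stronger assumption, so it should be paired with multiple imputation. Dropout of the kind illustrated above depends on the unseen outcome itself, and a missing-at-random method would not fully remove its effect. The sensitivity analysis should therefore vary the assumed risk among those missing.

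The cost is a few sentences of plan wording and slightly more analysis work. No new data, visits or participants are needed. The change should be made before outcome data are examined by arm.

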Four arms were designed in our research, including two intervention arms and two control arms. Participants in the two intervention groups will receive AIDS Fighter · Health Defense, one of which will strictly control the time spent in the game and provides incentives to increase motivation to use the game; Another group will receive AIDS Fighter · Health Defense, but without time limitation or incentives; One of the two control groups is classroom teaching and the other is autonomous learning. By comparing the intervention groups with the control groups, it can be found whether AIDS Fighter · Health Defense is better than classroom teaching and autonomous learning in improving participants’ AIDS prevention ability; By comparing the two intervention groups, we can figure out whether AIDS Fighter · Health Defense is attractive, whether players will voluntarily use the game to improve AIDS prevention capabilities. This will determine whether the game can be promoted on a large scale. By comparing the two control groups, we can understand the difference between classroom learning and autonomous learning in improving AIDS prevention capabilities. Such a design could see the differences in the effects of game-based intervention, classroom teaching, and independent learning in AIDS education. And provide evidence for choosing different AIDS education methods.

We hope that the game-based interventions can be widely used in AIDS education in China and other countries. However, some countries are exam-oriented in evaluating the effect of education and there may be some resistance to the promotion and application of the game; parents may worry that their children will be addicted to the game and affect their academic performance [26, 27]. To address this problem, we can perform identity authentication when the player enters the game and prevent minors from being addicted to the game by limiting the online time.

“AIDS Fighter · Health Defense” could be suitable for the public, high-risk groups of AIDS, and HIV-infected people. It could be an auxiliary educational tool for AIDS prevention for the public and high-risk groups, and for HIV-infected people to maintain long-term ART adherence and keep virus suppression. We believe that with the development of this study, we can provide an AIDS education method for China and other countries to improve the ability to prevent AIDS of public and the quality of life of HIV infected.

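### The hypotheses on risk behaviours are specific contrasts, but the test named for behaviours is an overall four-arm comparison whose P value answers neither of them

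*Protocol article*

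**What the plan says.** In the protocol article, Study design lists three hypotheses, all of which cover behaviour. The first expects the two game arms not to differ. The second is directed: compared with the controls, the game groups "will have More AIDS-related knowledge, less AIDS-related stigma and fewer AIDS-related risk behaviors". The third is also directed and compares the two controls: "group 1 will show better effects in improving AIDS-related knowledge, attitude and behaviors". The Discussion repeats these as three separate questions, for example: "By comparing the two control groups, we can understand the difference between classroom learning and autonomous learning".

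Data management and statistical analysis gives one sentence per outcome type. For knowledge and attitude scores, the ANOVA is to look for "differences between the AIDS Fighter · Health Defense intervention groups and the control groups in AIDS-related knowledge scores and attitude scores". For behaviours, the secondary outcome, the Repeated Measures ANOVA is to look for "differences on the incidence of AIDS-related behaviors followed up for three and six months after the intervention in four arms". The significance threshold is P ≤ 0.05. The behaviour sentence ties no contrast to any hypothesis.

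**The concern.** The null hypothesis of a four-arm comparison is that all four arms are equal. The second hypothesis needs a different null (game groups equal control groups), and so does the third (control group 1 equals control group 2). If the third hypothesis is true, as the protocol expects, the four-arm null is false whatever the game does. A significant P value would then be open to being read as support for fewer risk behaviours with the game when it came from the difference between the two controls. The four-arm test also spreads a one-degree-of-freedom question over three degrees of freedom, which costs power when the game does work.

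**Working it through.** **The plan's own figures.** Recruitment gives 131 per group, 10% attrition, 145 per group and 580 in total. 131 × 1.10 = 144.1, rounded up to 145; 131 / 0.90 = 145.6, rounded up to 146; 4 × 145 = 580. The stated numbers reproduce within one participant. After 10% loss, 145 × 0.90 = 130.5, so I use n = 130 per arm. No effect size, standard deviation or behaviour rate is given, so the plan's power for behaviours cannot be reproduced and everything below rests on assumed rates.

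**Set-up.** The outcome is a yes/no behaviour at two visits, with the same rate p at both and within-person correlation r of 0.5 or 0.7 (assumed). With complete data, the between-arm term of a two-visit repeated-measures ANOVA equals a one-way ANOVA on each person's mean.
- Variance of a person mean: s² = average of p(1−p) over the arms × (1+r)/2.
- Four-arm test: F with 3 and 4 × 129 = 516 df, critical value 2.62, noncentrality λ = n × Σ(p − mean p)² / s².
- Pooled contrast (mean of the two game arms minus mean of the two control arms): standard error √(s²/n), since the squared weights sum to 1.
- Game arms versus one control: standard error √(1.5 s²/n).
- Control 1 versus control 2: standard error √(2 s²/n).

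**Scenario A: controls differ, pooled game effect zero.** Rates are 15%, 15%, 10% and 20% (game 1, game 2, classroom, QQ).
- Average p(1−p) = (0.1275 + 0.1275 + 0.09 + 0.16)/4 = 0.12625, so s² = 0.0947 (r = 0.5) or 0.1073 (r = 0.7).
- Σ(p − 0.15)² = 0.005, so λ = 130 × 0.005 / s² = 6.87 or 6.06.
- Four-arm rejection from the noncentral F: 58% or 52%. Simulation gave about 53–58%.
- Pooled contrast: difference 0, so it rejects at its nominal 5%.
- Control 1 versus control 2, the direct test of the third hypothesis: 0.10/0.0382 = 2.62 or 0.10/0.0406 = 2.46 standard errors, so power is 74% or 69%.

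**Scenario B: game works equally against both controls.** Rates are 10%, 10%, 16% and 16%.
- Average p(1−p) = (0.09 + 0.1344)/2 = 0.1122, so s² = 0.0842 or 0.0954.
- λ = 130 × 4 × 0.03² / s² = 5.56 or 4.91. Four-arm power: 48% or 43% (simulation 42–49%).
- Pooled contrast: 0.06/0.0254 = 2.36 or 0.06/0.0271 = 2.21 standard errors. Power: 65% or 60% (simulation 59–67%).
- Game arms versus one control only: 0.06/0.0312 = 1.93 or 0.06/0.0332 = 1.81 standard errors. Power: 48% or 44%, no better than the four-arm test.

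**Sensitivity to the size of the control difference.** On a continuous scale with 131 per arm, and both game arms midway between the controls, the four-arm test rejects 24%, 51%, 64%, 78% and 94% of the time for classroom–QQ gaps of 0.2, 0.3, 0.346, 0.4 and 0.5 SD. The pooled contrast stays at 5%. A gap of 0.346 SD is the two-arm difference that 131 per arm detects with 80% power: √(2/131) × (1.960 + 0.842) = 0.346.

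**Calibration.** With all four arms equal, both tests reject about 5% in simulation.

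**The case against.** The strongest reply is that this is a condensed article. The phrase about four arms may only say which arms enter the model, and contrasts from that model may be set out in an analysis plan that is not shown. The Discussion lists the three comparisons separately. This has force against any claim that follow-up tests are missing, and none is made here. It does not remove the mismatch: the preceding sentence frames knowledge and attitude as intervention groups versus control groups, and the behaviour sentence asks a different question.

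Several stronger readings are tempting but are not supported:
- A reader might infer that the test rejects although the game has no effect against the controls. In scenario A the game is 5 points worse than classroom and 5 points better than QQ, so rejecting four-arm equality is correct. Only the pooled difference is zero. Nothing in the article predicts that the game will sit exactly at the control average.
- A reader might infer that the four-arm P value is to be the sole evidence for the second hypothesis. The article does not say so.
- A reader might object that an arm-by-time term over the 3- and 6-month visits cannot see an effect equal at both. The article never names that term as the test, and the between-arm term already averages over the two visits.
- A reader might expect two separate contrasts, game versus each control, to cure the problem. They do not gain power in scenario B. At least one of them rejects about 54–58% of the time in scenario A, and about 10% when all arms are equal.

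**Conclusion.** The point holds as a mismatch between the hypotheses and the test stated for behaviours. A significant four-arm P value does not by itself support either directed hypothesis. Under the assumed rates it arises about 53–58% of the time when the pooled game-versus-control difference is zero, and it gives up roughly 17 to 18 points of power (48% against 65%, or 43% against 60%, by the formulas above) when the game works equally against both controls. The sizes depend on assumed rates, correlations of 0.5 to 0.7 and 130 analysed per arm; the mismatch does not. The power advantage belongs to the pooled contrast only. The point concerns the secondary outcome, so it should be corrected but does not undermine the primary analysis.

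**What to change.** In Data management and statistical analysis, amend the behaviour sentence as follows:
- Name one pooled contrast, both game arms versus both control arms, as the test of the second hypothesis on behaviours. Take it from the between-arm effect averaged over 3 and 6 months, and report the difference with its 95% confidence interval.
- Name control group 1 versus control group 2 as the test of the third hypothesis, reported in the same way.
- Report the game arms against each control separately as supportive estimates.
- State that the overall four-arm P value alone is not evidence for the second hypothesis.

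The cost is a few lines of text and contrast statements from the same model, with no new data or participants. There are two small downsides: the pooled contrast averages over two different controls, which is why the separate estimates should sit beside it, and a significant overall P value can no longer be cited as success.
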